### Sample size determination

The required sample size was calculated using G*Power (version 3.1.9.7, Germany) for a two-way repeated-measures ANOVA (within-between interaction), with a significance level of α = 0.05, power (1–β) = 0.80, and four intervention groups (Control, RT, VT, RVT). The effect size was set to f = 0.40 (partial η^2^ = 0.14), which reflects a moderate-to-large effect based on prior studies assessing changes in IGF-1 expression and physical function following resistance and vibration training in older adults. The primary endpoint for power estimation was the change from baseline to 12 weeks, representing the completion of the supervised intervention. The 24-week point is considered a follow-up to assess sustainability but was not included in the power calculation. Considering a 20% dropout rate, the minimum required sample size was estimated at 73 participants [45]. Therefore, we plan to recruit 96 individuals (24 per group) to ensure adequate statistical power. In view of multiple primary outcomes and six pairwise comparisons among four groups, Holm–Bonferroni correction will be applied to adjust for potential inflation of type I error. Additionally, the hypothesis is based on additive rather than synergistic effects between RT and VT. Hence, interaction effects were not included in the sample size model but will be explored post hoc.

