### Statistical analysis

IBM SPSS v.20.0 will be utilized to analyze all the data. The primary outcomes will be assessed using two-way repeated-measures analysis of variance (ANOVA), with factors including time (baseline, 12 weeks, 24 weeks) and group (control, RT, VT, RVT). This approach was selected to allow direct estimation of group-by-time effects for predefined primary endpoints under a balanced design. Holm–Bonferroni adjustments will be applied for post-hoc pairwise comparisons. Missing data will be imputed via multiple imputation. Sex, along with baseline IGF-1, age, and muscle mass, will be included as covariates in analysis of covariance (ANCOVA) models to adjust for potential confounding effects. Effect sizes (partial η^2^ for ANOVA; for pairwise comparisons, the Cohen’s d with 95% confidence intervals were employed) will be categorized as small (η^2^ ≥ 0.01, d ≥ 0.2), medium (η^2^ ≥ 0.06, d ≥ 0.5), or large (η^2^ ≥ 0.14, d ≥ 0.8), accompanied by exact p-values. The 95% confidence intervals for Cohen’s d and model-based estimates will be calculated using either model-derived standard errors or the bias-corrected and accelerated (BCa) bootstrap method with 1,000 resamples, depending on distributional assumptions. To better accommodate repeated measures and potential within-subject correlations in secondary longitudinal outcomes, linear mixed-effects models will be used, incorporating random intercepts for participants and fixed effects for time, group, and their interaction. In addition, exploratory subgroup analyses stratified by sex will be conducted to evaluate potential sex-specific intervention effects. Subgroup interaction terms will be tested where appropriate, with p < 0.10 considered indicative of potential moderation. Statistical significance will be defined as p < 0.05 for all primary tests. Although the current sample size is not specifically powered to detect sex-based interaction effects, these exploratory analyses will inform the design of future sex-specific trials. All analyses will follow the intention-to-treat (ITT) principle. All randomized participants will be analyzed according to their assigned groups, regardless of protocol adherence or study completion status.

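### The sample size and analysis sections give the Holm correction different scopes, and the stated power is for one unadjusted test

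*Protocol article*

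**What the plan says.** The outcome measures section of the protocol article lists three primary outcomes: skeletal muscle mass, handgrip strength and 6-meter gait speed.

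Under Sample size determination, the calculation uses a "significance level of α = 0.05, power (1–β) = 0.80, and four intervention groups", for a within-between interaction. It also states: "The effect size was set to f = 0.40", "The primary endpoint for power estimation was the change from baseline to 12 weeks", and "Considering a 20% dropout rate, the minimum required sample size was estimated at 73 participants". The planned number is 96, or 24 per group. The same paragraph then says: "In view of multiple primary outcomes and six pairwise comparisons among four groups, Holm–Bonferroni correction will be applied".

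Under Statistical analysis, the primary outcomes are tested by two-way repeated-measures ANOVA, with the group-by-time effect as the quantity of interest. The multiplicity statement there is: "Holm–Bonferroni adjustments will be applied for post-hoc pairwise comparisons". Later in the paragraph, just after a threshold of 0.10 for subgroup interactions, comes: "Statistical significance will be defined as p < 0.05 for all primary tests".

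Neither section defines the Holm family (six pairs within each outcome, or 18 over all outcomes). Neither says whether a positive trial needs one, some or all of the three outcomes.

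**The concern.** The rule is stated twice with different scope. In the sample size section the multiple primary outcomes are part of the reason for Holm. In the analysis section, which will be followed when the data are analysed, Holm reaches only the pairwise comparisons, and nothing is said to adjust the three group-by-time tests against one another.

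Two analysts could both follow the article and disagree on whether a result is positive. Suppose one primary outcome has p = 0.03 and the other two are clearly null. It is significant under the literal analysis text. It is not significant under Holm across three outcomes, where the smallest p-value must be below 0.05/3 = 0.0167.

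The choice also affects the justification of the sample size, which spends the whole 0.05 on one test in the same paragraph that announces a correction.

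**Working it through.** **Inputs from the article:** three primary outcomes; four groups, hence 6 pairs and 3 × 6 = 18 pairwise comparisons; α = 0.05; f = 0.40; minimum N 73; planned N 96; dropout 20%, so 96 × 0.8 = 76.8, about 77 completers. **Assumed, because not stated:** the correlation between outcomes and the success rule.

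**1. Reproducing the plan's figure.** Take a noncentral F with λ = f²N and degrees of freedom 3 and N − 4. At N = 73, λ = 0.16 × 73 = 11.68. At α = 0.05 the power is 0.805, and 73 is the smallest N reaching 0.80. The stated figure is thus reproduced as one omnibus test, one outcome, unadjusted 0.05. In this form 73 is the number before dropout (73/0.8 = 91.25, so 92 recruited). The planned 96 still covers that, and it is a separate matter.

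**2. Familywise error of the literal analysis text.** Three tests at raw 0.05, success on any one, no true effect. If independent: 1 − 0.95³ = 0.143. For correlated outcomes: simulation of three four-group F tests, 24 per group, 40,000 trials per correlation. The last two columns apply Holm to the pairs without requiring a significant omnibus test first.

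| Correlation | Any omnibus p < 0.05 | Holm over 6 pairs, separately per outcome | One Holm family of 18 pairs |
|---|---|---|---|
| 0 | 14.4% | 11.8% | 4.3% |
| 0.3 | 13.7% | 11.3% | 4.1% |
| 0.5 | 12.8% | 10.5% | 4.0% |
| 0.7 | 11.4% | 9.6% | 3.8% |
| 0.9 | 8.3% | 7.1% | 2.7% |

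Pairwise Holm within each outcome therefore does not remove the multiplicity across outcomes. A Holm family that spans the outcomes does.

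**3. Power if Holm covers the three outcomes.** Same form, f = 0.40. The first Holm step uses 0.05/3; the second, reached once another outcome has succeeded, uses 0.05/2.

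| N contributing | λ = 0.16N | α = 0.05 | α = 0.05/2 | α = 0.05/3 |
|---|---|---|---|---|
| 73 | 11.68 | 0.805 | 0.714 | 0.658 |
| 77 | 12.32 | 0.829 | 0.744 | 0.691 |
| 96 | 15.36 | 0.912 | 0.855 | 0.817 |

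For 0.80 at 0.05/3 with equal groups, 96 evaluable participants are needed, or 96/0.8 = 120 recruited at 20% dropout.

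**4. Dependence on the form.** The article names a repeated-measures interaction. With two time points and within-person correlation ρ, λ = 2Nf²/(1 − ρ). At N = 73 and ρ = 0, λ = 23.36, and power is 0.985 at 0.05 and 0.957 at 0.05/3; it is higher for larger ρ. But this form needs only 39, 29, 22 or 15 participants for ρ = 0, 0.3, 0.5 or 0.7, so it does not reproduce 73.

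**The case against.** The strongest reply is that the two sections can be read together. The 0.05 sentence follows the 0.10 threshold for subgroup interactions and may serve only to separate primary from exploratory tests. It does not say raw p-values. Since the sample size section already commits to Holm because of the multiple outcomes, 0.05 could be the overall level for adjusted p-values, and the error would then be at most 5%. If all three outcomes had to be significant, there would be no inflation either. This stands as a possible reading, so a flat contradiction is not proven. But the article states neither condition, and the analysis section gives Holm a narrower scope than the sample size section does.

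Three stronger readings are tempting and are not supported:

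- *That the familywise error of this trial is 13–14%.* That needs raw p-values, success on any one outcome, and outcomes correlated at no more than about 0.5. The article fixes none of these.
- *That the 0.80 power fits neither rule.* It fits the literal analysis text: one omnibus test at 0.05 gives 0.805 at N = 73. Only the Holm rule is unmatched.
- *That power is simply too low.* The fall to 0.66–0.69 belongs to the form that yields 73. The analysis is by intention to treat with multiple imputation, so the information available lies between 77 completers and all 96. Nor does the article single out the combined group against either single training as the primary contrast, or state effects for individual pairs, so a power figure for those contrasts would rest on the reader's own assumptions.

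**Conclusion.** The point holds as an inconsistent and undefined multiplicity rule. It matters because it decides which primary results count as positive. Under the literal analysis text the familywise error is roughly 8% to 14%, depending on an assumed correlation from 0.9 down to 0. Under Holm across the outcomes it is at most 5%. The article leaves both open.

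The sample size justification supports one omnibus test at unadjusted 0.05 and does not account for the Holm rule announced beside it. In the form that reproduces 73, power at the first Holm step is between 0.69 (77 completers) and 0.82 (all 96 contributing), against the stated 0.80. Later Holm steps are less strict. A repeated-measures definition of f would give more power, but the stated 73 does not come from it.

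**What to change.** In Statistical analysis, keep the group-by-time test as the primary test and replace the 0.05 sentence with wording such as:

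> The three primary group-by-time tests are adjusted together by Holm–Bonferroni at an overall 0.05. Pairwise comparisons are tested only for outcomes significant at that step, with Holm over the six pairs. The 0.05 threshold applies to adjusted p-values.

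State the same rule in Sample size determination. There, say that 0.80 refers to one omnibus test at unadjusted 0.05, and add the power at the adjusted level, naming the form of the calculation.

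This rule holds the error at 5% over the three outcome-level claims. The pairwise claims are held at 5% within each outcome. When several outcomes show real effects, the error over all pairwise claims together is bounded only by 3 × 0.05 = 0.15. If control over all 18 pairs is wanted, a single Holm family of 18 provides it at a further loss of power; the sponsor should choose knowingly.

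The cost is a few sentences and a less favourable stated power, with no extra participants or data. The article reports that enrolment is continuing; the change should be made before any outcome data are examined by group.

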### Data collection and quality control

Before randomization, the characteristics of all the participants will be acquired during baseline evaluations. No data or information will be shared with third parties. Each participant will receive a unique identifier to ensure anonymity, and only personnel conducting statistical analyses will have access to the study database.

All investigators will undergo a comprehensive training program covering the intervention methods for each group, eligibility criteria, trial protocols, outcome measures, and accurate data recording. All practitioners will be certified rehabilitation therapists with at least 3 years of clinical experience in sports rehabilitation.

To increase adherence, participants will receive timely visit reminders and will incur no costs for assessments or treatments. Those who complete all study procedures will receive financial compensation.

### Assessment of adverse events and adherence

Adverse events occurring during the intervention will be systematically documented. Participants experiencing such events may withdraw from the trial at their discretion. Participant engagement with and adherence to the intervention will be assessed for each group. If a participant withdraws from the program, we will record the reason for withdrawal.

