## Methods and analysis

### Study design and grouping

This randomized controlled trial will identify the effects of RT combined with VT on the IGF-1/PI3K/AKT/FOXO3 axis in a population with sarcopenia. Participants will be screened for sarcopenia, as defined by the AWGS in 2019, and recruited based on eligibility criteria. Fig 1 summarizes the participant’s enrollment process, interventions, and assessment schedule. Once informed consent is received, the participants will be randomly categorized into (1) control, (2) RT, (3) VT, and (4) combined RT and VT (RVT) groups. Intervention will last 12 weeks, with data collection and assessments at baseline, 12-week (after intervention), and 24-week (follow-up). The 12-week intervention duration was selected based on existing literature indicating that this time frame is sufficient to induce meaningful improvements in muscle mass, muscle strength, and molecular signaling among older adults. Prior studies on resistance and vibration training for sarcopenia typically range between 8–12 weeks, with 12 weeks allowing both early neural adaptation and later-stage hypertrophy to manifest [41–43]. The 24-week time point (i.e., 12weeks post-intervention) was included to evaluate the sustainability of training-induced benefits. Similar follow-up durations have been adopted in previous sarcopenia trials to assess the persistence or decay of functional gains after supervised training ends [44]. Muscle strength, mass, physical performance, FOXO3 protein expression levels, and quality of life will be assessed in all participants. Fig 2 depicts the study design, and S1 File contains the SPIRIT checklist.

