#### Educational courses.

Participants in the control group will attend a 60-minute education session twice monthly. Invited experts will deliver these sessions, covering topics such as aging, general health, and sarcopenia—including its definition, etiology, pathophysiology, clinical manifestations, and adverse effects in older adults. These educational courses are intended primarily to maintain participant engagement and minimize dropout. The sessions are standardized, lecture-based, and non-interactive, and do not include individualized exercise prescriptions or dietary counseling. Although it cannot be entirely excluded that exposure to health information may raise awareness or induce minor behavioral changes, previous studies have shown that education-only interventions in older adults generally do not lead to significant improvements in muscle strength, skeletal muscle mass, or physical function [55,56]. Therefore, the risk of overestimating the effects of exercise-based interventions due to this educational component is considered minimal.

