#### Secondary outcomes.

IGF-1 concentrations will be assessed *via* an enzyme-linked immunosorbent assay (ELISA) kit (IGF-1 600 ELISA; DRG, Germany). Blood will be collected from the antecubital vein in a fasting state in serum separator tubes, centrifuged for 15 minutes at 3000 × g and 4°C to harvest serum, which will be stored at −80°C for biochemical analysis [57].

The PI3K/AKT signaling pathway and FOXO3 protein activity will be assessed using immunoblotting (Western blot) and cell isolation assay on specimens obtained via muscle biopsy. Muscle biopsies will be collected at three time points: baseline (pre-intervention), 12 weeks (post-intervention), and 24 weeks (follow-up), enabling longitudinal analysis of the IGF-1/PI3K/AKT/FOXO3 axis. Although more frequent sampling could provide a finer-grained understanding of molecular responses, ethical and practical concerns regarding repeated invasive procedures in older adults limit the feasibility of acute or intra-intervention biopsies in this study. The percutaneous muscle biopsy technique will be employed for lateral femoral muscle biopsy. Briefly, after 2–3 mL of 1% dimethocaine local anesthesia, aspiration will be performed. Then, about 50 mg of muscle tissue lacking blood vessels and connective tissues will be dissected. The samples will be immediately placed in cryotubes, frozen in liquid nitrogen, and stored at −80°C [58].

Then, the protein content will be evaluated *via* the bicinchoninic acid assay (BCA) method (Pierce, Appleton, WI, USA). Subsequently, equal amounts of protein will be subjected to 12% SDS-PAGE gel electrophoresis and transferred onto PVDF membranes, which will then be treated at 4°C with the primary antibodies against PI3k (ab140307,1:1000, Abcam, UK), Akt (SAB4500797, 1:1000, Sigma, USA), Akt (phospho T308) (ab38449, 1:1000, Abcam, UK), and FOXO3 (SAB2107951, 1:1000, Sigma, USA) overnight. Next, the membranes will be flushed with phosphate-buffered saline with tween (PBST), probed with the HRP-linked specific goat anti-rabbit IgG secondary antibody (ab150077, 1:3000, Abcam, UK) for 2 h at ambient temperature, and then washed thrice with PBST. The bands will subsequently be quantified *via* the Image Lab system (Bio-Rad, Shanghai, China) [59,60]. The above analyses will be performed in the Sports Medicine Key Laboratory of Sichuan Province.

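### The stated adverse-event window covers only the 12-week intervention, while all three muscle biopsies and weeks 12 to 24 fall outside it, so harm reporting would be incomplete

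*Protocol article*

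**What the plan says.** The section on assessment of adverse events and adherence contains the article's one statement on collecting harms: "Adverse events occurring during the intervention will be systematically documented". It adds that adherence will be assessed in each group and that the reason will be noted if a participant withdraws from the program.

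The section on study design and grouping sets the timing: "Intervention will last 12 weeks, with data collection and assessments at baseline, 12-week (after intervention), and 24-week (follow-up"). It also explains the last visit: "The 24-week time point (i.e., 12weeks post-intervention) was included to evaluate the sustainability of training-induced benefits".

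The secondary outcomes section schedules the tissue sampling: "Muscle biopsies will be collected at three time points: baseline (pre-intervention), 12 weeks (post-intervention), and 24 weeks (follow-up"). On method it says: "The percutaneous muscle biopsy technique will be employed for lateral femoral muscle biopsy", under local anesthesia and taking about 50 mg of tissue. It explains why there is no sampling in between: "ethical and practical concerns regarding repeated invasive procedures in older adults limit the feasibility of acute or intra-intervention biopsies in this study". The limitations in the Discussion repeat the same three time points.

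On numbers, the sample size section says "we plan to recruit 96 individuals (24 per group) to ensure adequate statistical power" and allows for 20% dropout. Participants are aged 65 to 80 years.

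**The concern.** The harms sentence names a period, and no biopsy is scheduled inside that period. The biopsies are the most invasive thing done to participants, and the article itself treats their invasiveness as a reason to limit how many are taken. Yet the rule for recording harms is tied to the exercise or education phase rather than to study participation.

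The same sentence also leaves out the second half of the study. The week-24 visit exists to see whether benefits last, so as written the plan follows benefit for 24 weeks and systematically records harm for 12.

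At stake is whether the final report can say anything complete about biopsy complications or about events that appear after training ends. Someone planning a similar mechanistic trial in older adults would want that information.

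**Working it through.** This is a comparison of texts, with a simple count to give the size. The article states no figure for harms or biopsies that could be reproduced.

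**1. The window.** Adverse events are recorded during the intervention (adverse events section). The intervention lasts 12 weeks (study design section). No other section gives a different or wider window for adverse events.

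**2. The biopsies against the window.**

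| Biopsy | Article's label | Position relative to the window | What the stated rule would record |
|---|---|---|---|
| Baseline | Pre-intervention | Before | Only complications that appear or persist once the intervention has begun |
| Week 12 | Post-intervention | After | Nothing, unless the harm leads to a recorded withdrawal |
| Week 24 | Follow-up, 12 weeks after the intervention | After | Nothing, unless the harm leads to a recorded withdrawal |

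The article says sampling within the intervention is not feasible, so no further biopsy falls inside the window.

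**3. Number of biopsies.** Inputs: 96 participants, three biopsies each, 20% dropout (all from the article).

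- Full retention: 96 x 3 = 288.
- All dropout before week 12 (my assumption; the article does not say when dropout occurs): 96 x 0.80 = 76.8, about 77 remaining, giving 96 + 77 + 77 = 250.

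So about 250 to 288 biopsies are planned, and none is performed inside the stated window. Of these, the week-12 and week-24 biopsies number 77 + 77 = 154 to 96 + 96 = 192. For the 96 baseline biopsies, only the immediate harms are left out.

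**4. Time covered.** 12 of 24 weeks, or 50%. Weeks 12 to 24 are outside the window for events of any cause.

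**The case against.** The strongest reply is that the sentence commits to recording events in one period and does not say that others go unrecorded. This is a journal article. Its schedule figure and its supplementary files (the SPIRIT checklist and the ethics files) are not shown here, and they could set a wider window. Collection forms and procedural harms are often left to a full protocol. This stands as a limit on certainty about what will happen in practice. It does not remove the point, because the article does not stay silent: it states a window, and that window misses its own biopsy schedule. If a fuller document is wider, the article misdescribes the plan and still needs correcting.

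Three stronger readings are tempting, and the documents do not support them.

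- A reader might infer that no biopsy harm could ever be reported. That goes too far. A baseline complication that appears or persists after training starts falls inside the window. The instruction to note reasons for withdrawal carries no time limit, so a biopsy harm that makes someone leave the program could be captured.
- A reader might infer unequal ascertainment between arms, since exercise participants attend 3 x 12 = 36 sessions while for controls "Participants in the control group will attend a 60-minute education session twice monthly", about 6 over 12 weeks. Those are training and lecture contacts, not adverse-event enquiries. Nothing says that events are collected at either or that recording is unprompted, and the article describes the documentation as systematic.
- A reader might infer that the trial's safety conclusion would be wrong. The article lists no safety endpoint and plans no between-group safety comparison. All four groups follow the same biopsy schedule, so incomplete recording of biopsy harms would not by itself bias a comparison of the exercise programs.

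It is also fair to say that 288 is a ceiling, and that the documents give no complication rate from which to estimate the number of harms missed.

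**Conclusion.** The point holds as a badly set recording window. Followed literally, the article's rule omits immediate harms of the baseline biopsy, harms of the 12- and 24-week biopsies that do not lead to a recorded withdrawal, and all other events in weeks 12 to 24. The result is incomplete harm reporting, chiefly for the biopsies.

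The size is about 250 to 288 procedures and half of the scheduled 24 weeks. The lower count assumes that the 20% dropout all happens before week 12. The conclusion also assumes that no document outside the article extends the window. The efficacy and mechanistic analyses do not depend on this. The change is still worth making because it is cheap and recruitment is expected to run to 30 April 2026.

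**What to change.** Reword the sentence so that adverse events are recorded in all four groups from the first study procedure, the baseline biopsy, through a brief check after the week-24 biopsy. Use the existing assessment visits and the reminder contacts already planned. Report biopsy-related events separately from training-related events, so that a complication of sampling is not read as an effect of exercise or lost in a combined total. If a fuller document already provides for this, the article should say so and give the window.

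The study began on 30 April 2024, so the change cannot be fully prospective. For participants already enrolled, apply the wider window from now on, collect earlier biopsy events retrospectively where possible, and mark them as retrospective in the report.

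The cost is a protocol amendment, a few minutes per participant at existing contacts, and one additional short contact after the last biopsy. The change concerns recording only and alters no treatment, procedure or clinical rule.
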